**Fig. 1 Fig1:**
[figure not shown]
Flow diagram summarizing flow of participants through study phases

### Randomization, blinding and allocation concealment

Eligible participants will be randomised to receive either i) exercise alone or ii) diet plus exercise. The randomization schedule will be computer-generated and prepared by an independent biostatistician. The first list will randomly allocate participants to a physiotherapist (no strata). The second list will randomly allocate participants to an intervention group using variable permuted block sizes and a randomization ratio of 1:1, stratified by physiotherapist and participant sex (due to sex differences in weight gain, weight loss, and attitudes to weight loss [41, 42]). If a physiotherapist is unavailable (e.g. sick, on holiday) participants will be re-randomized to another available physiotherapist using a third list with variable permuted block sizes and stratified by group allocation and sex. The randomization schedule will be stored on a password-protected website (REDCap™) at the University of Melbourne and maintained by a researcher not involved in either participant recruitment or administration of primary/secondary outcome measures. Group allocation is revealed by this same researcher after completion of baseline assessment.

The components of each intervention will be disclosed to participants prior to enrolment as we wish to test the interventions under real world conditions whereby consumers are fully informed about their treatment components before choosing whether they wish to participate. The research staff member collecting non self-reported outcome measures (including the primary outcome) at 6 months will be blinded to group allocation and will be a different person from the one collecting baseline data. This is necessary given that obvious weight loss has the potential to unblind the assessor if baseline and 6 month measures were to be collected by the same person. It is not possible to blind physiotherapists as they are providing interventions to participants in both trial arms to ensure physiotherapist-related factors such as personality or clinical experience are similar between groups and cannot confound results. The statistical analysis plan will be written and published while the biostatisticians are blinded.

### Physiotherapists and training

We will use our network of physiotherapists and advertisements in the Australian Physiotherapy Association fortnightly e-news bulletin to recruit six practicing musculoskeletal physiotherapists working in private practice in Melbourne, Australia. These physiotherapists will deliver care to participants randomized to both trial groups. Eligibility criteria for the physiotherapists to deliver the interventions in this trial are:Current registration to practice as a physiotherapist with the Australian Health Practitioner Regulation Agency;A receptionist at their clinical practice to facilitate participant bookings and communication with research staff;An Australian Business Number;Willing to undertake trial training requirements;Willing and available to deliver interventions until the anticipated completion of the trial.

Mandatory comprehensive training (estimated total time commitment of 20 hours) will be undertaken by physiotherapists prior to them being allocated a trial participant. The training components include:Bespoke self-directed e-learning modules (on the University of Melbourne Learning Management System) covering: best practice OA management; strengthening exercises and physical activity prescription including the structured trial protocol and resources for use in the exercise component; the link between overweight/obesity and OA; having a weight loss conversation; weight stigma in physiotherapy; lifestyle and dietary interventions for weight loss; background to the ketogenic VLCD and the structured trial diet intervention protocol including safety issues; behaviour change support techniques and motivational interviewing techniques to promote adherence as well as resources for use in the diet component; telehealth (including delivery of care via Zoom video-conferencing), and study procedures including consultation structure. Physiotherapists will be told it will take approximately 10–12 hours to work through all e-learning modules, which they are encouraged to complete at their own pace over 6 weeks. The general e-learning modules (not specific to the study procedures) have since been adapted, and released for widespread use by clinicians outside of the trial and access is available to users globally:

(www.futurelearn.com/courses/eduweight).Six videoconference consultations to deliver sessions 1, 2 and 4 (one week apart) of the diet plus exercise program to one ‘mock’ patient (one of the research team) and one ‘practice’ patient with knee OA (recruited from our network). The sessions will be audiotaped. The researcher will provide feedback to the physiotherapist on competency in telehealth delivery and adherence to the protocol using a checklist of 60 items. The researcher will also discuss the consultations with the practice patient and provide feedback to the physiotherapist from the patient’s perspective.Teleconference(s) with the trial coordinator and a trial dietitian to answer any questions and clarify any study procedures with an estimated time commitment of one hour.

A hard copy of a “Physiotherapist Manual” detailing intervention protocols and study procedures, along with a hard copy of each of the participant resources, will be provided to each physiotherapist for their own reference and to facilitate study consultations.

### Interventions

Participants in both groups will consult a physiotherapist using the videoconferencing facility of Zoom (Zoom Video Communications, Inc., USA) for six individual sessions over 6 months. The consultations are recommended to occur in weeks 1, 3, 7, 11, 15 and 19, but the precise timing can be decided between each participant and their physiotherapist. Research staff will book the first two appointments on behalf of participants. Thereafter, physiotherapists will negotiate with participants to book follow-up consultations. The same physiotherapist will ideally undertake all consultations with any given participant. Before their first consultation with the physiotherapist, participants will complete a pre-consultation survey online asking about their main problems and goals, a brief history of their knee symptoms, weight and diet patterns (for the diet plus exercise group), and other health problems. All participants will also be provided with hard copy OA educational resources, activity booklets and log books, and resistance bands to facilitate their engagement with their program. Resources provided to both groups are detailed in Table 1.

**Table 1 Tab1:** Summary of resources provided to participants in the Exercise group and Diet plus exercise group

Resource	Description	Exercise group	Diet plus exercise group
Exercise resistance bands	4 exercise resistance bands (red, green, blue, black) to increase resistance for strengthening exercise	✓	✓
Formulated meal replacements	14 weeks of Optifast (or Optislim if vegetarian or Optifast unavailable) meal replacement products for ketogenic VLCD		✓
Plastic portion plate	Visual aid to manage portion sizes		✓
**Booklets**			
Preparing for your consultations	Information about consultations, instructions about how to download and use Zoom video conferencing	✓	✓
Exercise booklet	Step-by-step photographs and instructions for strengthening exercises for quadriceps, hip abductors, hamstrings, gluteal and calf muscles and balance exercises	✓	✓
Knee plan and log book	Workbook containing templates to detail agreed exercise plan and to track exercise sessions completed each week	✓	✓
OA information	Evidence-based information covering understanding OA, management options, misconceptions, pain coping skills and sleep	✓	✓
Weight management “how to” guide	Information on how to undertake the VLCD and how to transition from VLCD to normal healthy eating		✓
Weight management activities	Workbook containing behavioral support activities including finding a support person, tracking weight, identifying eating triggers, changing thought patterns, monitoring hunger levels and overcoming barriers		✓
Recipe book	A selection of ~ 75 recipes suitable for low glycaemic index carbohydrate meals or VLCD		✓
Food list pocket guide	Laminated list of low carbohydrate whole foods appropriate to eat during the ketogenic VLCD		✓

#### a) Exercise program

Physiotherapist consultations for participants in this group will last 30 minutes initially and 20 minutes thereafter. Physiotherapists will prescribe a home strengthening exercise program to be performed by the participant at home three times per week. The exercise program was used previously and shown to be effective [34, 43, 44]. The program will include 5–6 strengthening exercises from a pre-determined list including two quadriceps exercises, one each for the hip abductors, hamstrings and calf muscles, and any other exercise as appropriate from the list (Table 2) [43–46]. Participants will be asked to exercise at a moderate intensity (self-perceived effort of ≥5 out of 10 (hard) on a modified Borg Rating of Perceived Exertion scale [47]). So that they can provide real-time demonstration of exercises to participants during the videoconferencing consultations, using the share-screen feature of Zoom, physiotherapists are given access to a bespoke website containing a video library of exercises contained within the “Exercise Booklet”. The physiotherapist will also prescribe and support a personalized and progressive physical activity plan in collaboration with the participant. The physiotherapist will help the participant to identify barriers to exercise and possible solutions, advise on how to self-monitor and manage any pain flare-ups, and review, modify and progress the program as appropriate.

**Table 2 Tab2:** Strengthening exercise protocol, with instructions and progressions where applicable. Reprinted from: Hinman RS, Kimp AJ, Campbell PK, Russell T, Foster NE, Kasza J, Harris A, Bennell KL: Technology versus tradition: a non-inferiority trial comparing video to face-to-face consultations with a physiotherapist for people with knee osteoarthritis. Protocol for the PEAK randomised controlled trial. BMC Musculoskelet Disord 2020, 21(1):522 [45]

Home exercise protocol			
**Maximum of 6 exercises** (with progression as appropriate) performed three times a week - 2 knee extensor strengthening exercises - 1 hip abductor strengthening exercise - 1 hamstring strengthening exercise - 1 calf strengthening exercise - 1 other exercise as appropriate from the list (optional) **Dosage** Determined on an individual basis by the physiotherapist			
**1. Quads strengthening (aim to include two exercises)**			
**Knee extension**	Non weight-bearing	Q1. Seated knee extension (with resistance) with 5 s hold	**Progression:** Increase with theraband resistance – red through to black
	Non weight-bearing	Q2. Inner range quads over roll (with resistance) with 5 s hold	**Instruction:** Put a rolled up towel under your arthritis knee. Keep the knee cap and toes pointing toward the roof. Keeping the back of the knee in contact with the towel, push the back of your knee down into the towel and straighten your arthritis leg
**Sit-to-stand**	Weight-bearing	Q3. Sit to stand (without using hands)	**Progression:** lower chair height, hover above the seat without touching down (3 s hold), add resistance band around knees and push outwards keeping knees over toes
	Weight-bearing	Q4. Sit to stand with more weight on involved knee	**Instruction:** Take more weight by either a) placing uninvolved further forward b) shift both feet sideways so study leg is midline
**Steps**	Weight-bearing	Q5. Step-ups	**Progression:** Increase step height
	Weight-bearing	Q6. Forward touchdowns from a step	**Progression:** Increase step height, don’t touch floor
	Weight-bearing	Q7. Step-ups with weight	**Instruction:** Hold 2 kg of weight either a) against chest, b) in each hand, c) in one hand while holding for balance, or d) in backpack **Progression:** Increase step height, increase weight
	Weight-bearing	Q8. Forward touchdowns from a step with weight	**Instruction:** Hold 2 kg of weight either a) against chest, b) in each hand, c) in one hand while holding for balance, or d) in backpack **Progression:** Increase step height, increase weight
**Wall squats**	Weight-bearing	Q9. Partial wall squats for 5 s hold	**Progression:** more weight on study side
	Weight-bearing	Q10. Split leg wall squats for 5 s hold	**Instruction:** Step feet away from wall (about 30 cm) and move non-involved leg a further 15 cm away from the wall.
**Controlled squats**	Weight-bearing	Q11. Controlled partial squat with 5 s hold	
**Leg Sliding**	Weight-bearing	Q12. Forward and backward sliding of non-study leg	**Instruction:** Keep weight on study leg. Concentrate on keeping knee positioned over the foot
	Weight-bearing	Q13. Forward and backward sliding of non-study leg with resistance band pulling study leg laterally	**Instruction:** Place loop of elastic band around involved knee and leg of a table to provide a pull outwards on knee that you must resist by keeping knee in line with foot. **Progression:** Increase with theraband resistance – red through to black
	Weight-bearing	Q16. Sideways sliding of uninvolved leg	**Instruction:** Keep weight on study leg. Concentrate on keeping knee positioned over the foot
	Weight-bearing	Q17. Sideways sliding of uninvolved leg with resistance band pulling study leg laterally	**Instruction:** Place loop of elastic band around study leg and leg of a table to provide a pull outwards on knee that you must resist by keeping knee in line with foot. **Progression:** Increase with theraband resistance – red through to black
**Step to single leg balance**	Weight-bearing	Q14. Step with study leg to about 30° knee flexion for single leg balance	**Instruction:** Take a step forwards with study leg, keeping knee bent to about 30° knee flexion. Allow uninvolved leg to lift off and practice balancing as long as you can
	Weight-bearing	Q15. Step with study leg to about 30° knee flexion for single leg balance with arm movements	**Instruction:** Take a step forwards with involved knee, keeping knee bent to about 30° knee flexion. Allow uninvolved leg to lift off and practice balancing as long as you can, while raising arms out to side and above head in an arc.
**2. Hip abductor strengthening (1 exercise)**			
**Standing hip abduction**	Weight-bearing	HA1. Side leg raises in standing with 5 s hold	**Progression**: Increase theraband resistance – red through to black, add another 5 s halfway
**Side stepping**	Weight-bearing	HA2. Crab walk with resistance band	**Progression:** Increase theraband resistance – red through to black
**Standing hip abduction**	Weight bearing	HA3. Wall push standing on study leg for 20 s	**Progression:** Hold weight in hand, increase the hold time
	Weight bearing	HA4. Wall push standing on study leg positioned up to 45° knee flexion	
**3. Hamstring strengthening (1 exercise)**			
**Bridging**	Weight-bearing	HG1. Bridge with 5 s hold	
	Weight-bearing	HG2. Split leg bridge with 5 s hold	**Instruction:** Place feet hip-width apart, then move study leg slightly closer toward your bottom and slightly in towards centre
	Weight-bearing	HG3. Single-leg bridge on study leg with 5 s hold	**Version A:** Lift bottom. Keeping hips level, lift uninvolved leg off the floor/bed. Hold for 5 s. Slowly lower uninvolved leg back to the floor. Then slowly lower bottom back to floor. **Version B:** Lift uninvolved knee off floor/bed. Lift bottom and take all weight through study leg. Hold for 5 s. Slowly lower your bottom back to floor/bed.
**Standing knee flexion**	Non weight-bearing	HG4. Hamstring curls -Standing over bench knee flexion with 5 s hold	
	Non weight-bearing	HG5. Hamstring curls -Standing over bench knee flexion with 5 s hold against resistance band	**Instruction:** Place one end of an elastic band securely around ankle of study knee. Place the other end of elastic around your opposite foot so you are standing on it.
**Seated knee flexion**	Non weight-bearing	HG6. Seated knee flexion	**Instruction:** Place one end of an elastic band securely around a stable object (e.g. a heavy table leg). Loop the other end around the ankle of your study leg. Keeping your opposite foot on the floor, pull against the elastic band and bend your knee more. **Progression:** Increase with theraband resistance – red through to black
**Standing hip extension**	Non weight-bearing	HG7. Hip extension with knee bent (90°) - standing over bench with 5 s hold	
	Non weight-bearing	HG8. Hip extension with knee straight - standing over bench with 5 s hold	
	Non weight-bearing	HG9. Hip extension with knee straight with resistance band - standing over bench with 5 s hold	**Instruction:** Place one end of an elastic band securely around ankle of study knee. Place the other end of elastic around your opposite foot so you are standing on it.
**4. Calf strengthening (1 exercise)**			
**Standing plantar-flexion**	Weight-bearing	C1. Double heel raises with 5 s hold	
	Weight-bearing	C2. Single heel raises with 5 s hold	
	Weight-bearing	C3. Double heel raises with 5 s hold over edge of step	
	Weight-bearing	C4. Double heel raises with 5 s hold over edge of step	
**5. Balance exercises**			
**Tandem stance**	Weight- bearing	B1. Maintain balance in tandem stance	**Progression:** remove hand support, slowly raise arms in the air, eyes closed
**Natural stance**	Weight- bearing	B2. Maintain balance whilst tapping opposite foot forwards & backwards	
**Single leg stance**	Weight- bearing	B3. Maintain balance in single leg stance	**Progression:** Increase hold time, slowly raise arms up and down, eyes closed

#### b) Diet plus exercise program

Physiotherapist consultations for participants in this group will last 75 minutes initially (30 minutes for the exercise component and 45 minutes for the diet component) and 50 minutes thereafter (20 minutes for the exercise component and 30 minutes for the diet component). The exercise components for this group are the same as those described above for the exercise only program.

The physiotherapist will support the participant to lose weight (aiming for ≥10% body weight loss) via a ketogenic VLCD, with additional dietary/behavioural educational resources provided in hardcopy [34] (Table 1). Ahead of their initial consultation, participants will be sent approximately 4–5 weeks of meal replacement products from the Optifast product range (Nestlé Health Science, Rhodes, Australia). In cases where Optifast products are out of stock, or the participant cannot tolerate or does not wish to consume products containing fish oil, Optislim meal replacements are provided as an alternative (Optipharm, Australia). Participants will be asked to register their product and flavour preferences for each of their orders. Meal replacements will continue to be supplied at no cost to the participant for a maximum of 14 weeks.

Participants will collaboratively develop a weight management plan and a weight loss goal with their physiotherapist during their initial consultation. Physiotherapists will ask participants to substitute two of their normal meals each day with meal replacement products, with the participants able to choose which meal they substitute with which product. For their third meal of the day, participants are asked to consume a low carbohydrate, low fat meal, consisting of high-quality protein (e.g. meat/fish/eggs/tofu), non-starchy vegetables, and (for participants who have not had their gall bladder removed) the equivalent of a tablespoon of unsaturated fat (e.g. olive oil/ nuts/avocado). Importantly total caloric intake should be approximately 800 kcal (3280 kJ) per day and carbohydrate intake should not exceed 50–60 g per day. Modifications of the diet will be permitted as necessary in instances where participants are unwilling to stick to the diet as prescribed. In such cases, caloric restriction and low carbohydrate intake will continue to be advised. Participants will be encouraged to track their weight on a weekly basis and are provided space to do so in their weight management activities booklet.

During the subsequent five consultations, participants will self-report their progress, and any challenges or difficulties they have experienced with their weight management plan. Physiotherapists will use motivational interviewing techniques to help encourage self-efficacy and motivation, and collaboratively develop ways to help the participant overcome their barriers. Physiotherapists will encourage participants to engage with activities in the booklets including setting realistic goals; keeping a food diary; identifying a suitable support person; identifying eating triggers; developing strategies to deal with challenging situations and monitoring and mindfulness of hunger levels, as well as discussing education topics such as healthy foods and portion sizes.

Physiotherapists will support participants in deciding when to transition off the ketogenic VLCD, first raising the discussion when they have achieved 10% weight loss, or once they have been on the ketogenic diet for 12 weeks, whichever comes first. During the two-week transition phase, participants will be asked to consume only one meal replacement per day and to gradually reintroduce low glycaemic index carbohydrates to their other meals. After the two week transition phase, participants will enter the weight maintenance phase in which they will be asked to eat a healthy whole food diet, focusing on meals which are high in protein, low in fat and with low glycaemic index carbohydrates, as recommended by the Commonwealth Scientific and Industrial Research Organisation Total Wellbeing diet [48]. Participants will receive verbal education and support from the physiotherapist during their remaining physiotherapy consultations to maintain their weight loss. The hard copy resources which they keep once their involvement in the study is complete also contains this information. Participants will be advised by the physiotherapist to continue monitoring their weight on a weekly basis, and if they gain 2 kg or more, to return to the ketogenic VLCD for 1–2 weeks.

Meal replacements will be provided to participants at no cost for the first 14 weeks of the study.

After this time, meal replacements will be self-sourced and self-funded if participants opt to re-engage with the ketogenic VLCD. Participants will be offered strategies and resources during the program, which will assist their long-term weight maintenance after their consultations with the physiotherapist are completed, including regular weight monitoring and dealing with setbacks [34].

### Outcome measures

Body weight will be measured at baseline and 6 months on the same set of calibrated digital high capacity scales (Seca 813). Weight will be reported in kgs to two decimal places. Change in body weight, expressed as a percentage, is the primary outcome.

There are a number of secondary outcomes. These are measured at baseline and 6 months, unless otherwise stated, and include:i)BMI in kg/m^2^;ii)Waist circumference at mid-abdomen level at its smallest circumference in cm;iii)Waist-to-hip ratio by dividing the waist circumference by the hip circumference at its widest part;iv)Self-reported average knee pain on walking in the last week measured using an 11-point NRS with terminal indicators of ‘no pain’ = ‘0’ and ‘worst pain possible’=‘10’ [49];v)Intermittent and constant osteoarthritis pain measure (iCOAP) [50] with 11 items using a 4-point Likert scale and subscales for constant pain (scored 0 to 20) and intermittent pain (scored 0 to 24). Higher scores indicate higher levels of pain;vi)Physical function subscale of the Western Ontario and McMaster Universities Osteoarthritis Index (WOMAC) [51] scored over 17 items, using a 4-point Likert scale with a total score between 0 and 68. Higher scores indicate more severe dysfunction;vii)Perceived global change in knee problems scored on a 7-point Likert scale from ‘much worse’ to ‘much better’ [52] at the 6-month time point only. Participants who indicate that they are “moderately better” or “much better” will be categorized as ‘improved’. All other respondents will be categorized as ‘not improved’;viii)Health-related quality of life using the Assessment of Quality of Life (AQoL) (version AQoL-6D) [53], a 20-item instrument with scores ranging between − 0.04 to 1.0 and higher scores indicating higher quality of life;ix)Physical activity levels evaluated using the physical activity scale for the elderly (PASE) [54] with scores from 0 to 400 with higher scores indicating greater levels of physical activity;x)Weight Self-Stigma Questionnaire (WSSQ) to evaluate internalized weight stigma [55] reported via two subscales (self-devaluation and fear of enacted stigma) and a combined total of 0–60 with higher scores indicating greater internalized weight stigma;xi)Physical performance measures recommended by the Osteoarthritis Research Society International [56] and assessed by a researcher blinded to group allocation;30s chair sit-to-stand test: The number of complete chair stands achieved in 30s will be reported [56]. Higher scores indicate better physical function.40 m fast-paced walk test: The total time taken to walk 40 m quickly but safely will be recorded, and reported in speed (m/s) [56]. Faster walking speeds indicate better physical function.6-step stair climb test: The total time taken to ascend and descend a flight of six stairs will be recorded [57]. Use of the handrail is optional. Shorter completion times indicate better physical function.xii)Maximum voluntary isometric strength of the knee extensors measured on an isokinetic dynamometer (HUMAC, CSI, Boston) with the knee held at 60 degrees flexion. The maximum torque reached over 3 repetitions of 5 seconds, normalized to body mass, will be recorded in Nm/kg.

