While knee OA clinical guidelines recommend weight loss [14, 15], they do not specify how best to do this or which dietary approach to use. There is evidence to show that very low calorie diets (VLCDs) involving meal replacements are more effective for inducing significant weight loss and improving physical function than diets that involve lifestyle counselling alone in people with knee OA [29]. Ketogenic VLCDs, whereby carbohydrate intake is additionally restricted (< 50-60 g per day), have also been demonstrated to be an effective and safe means of achieving rapid weight loss in the adult population with overweight and obesity [30] and lead to greater weight loss than low-fat diets in the short-term [31]. An advantage of a ketogenic diet is possible reduction in hunger [32, 33], a feature that may assist with adherence to caloric restriction. The predicted rapid weight loss of 1.5–2.5 kg per week [31] means that those adhering to a ketogenic VLCD frequently achieve a 10–15% weight loss target weight within 12 weeks, an amount likely to have symptomatic benefits for people with knee OA [13].

In a recent randomized controlled trial (RCT), we tested the effectiveness of a telehealth program comprising a ketogenic VLCD delivered by dietitians and exercise delivered by physiotherapists for people with knee OA. The trial showed that this combined program led to greater improvements in pain and function, as well as greater weight loss, when compared to an exercise-only program and to online education control [34]. In our qualitative research, participants described positive experiences with the ketogenic VLCD program, valuing its simplicity and effectiveness [35]. Support from dietitians and a comprehensive suite of educational and behaviour change resources, incorporated with an exercise program, were considered crucial for weight loss success. The telehealth delivery mode was valued for its convenience [35, 36], particularly time efficiency and access. The protocolized and nutritionally complete manner of the ketogenic VLCD using meal replacements means that healthcare practitioners without formal nutrition qualifications, such as physiotherapists, may be capable of effectively and safely supporting such a VLCD for some people with knee OA.

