This trial aims to evaluate the effectiveness of a 6-month telehealth physiotherapist-delivered ketogenic VLCD added to exercise compared with telehealth physiotherapist-delivered exercise alone in people with knee OA who have overweight/obesity. The primary hypothesis is that the group offered the diet plus exercise program will lose more weight than the group offered an exercise only program at 6 months. The trial will also evaluate effects on secondary outcomes including body mass index, weight circumference, waist-to-hip ratio, knee pain, physical function, global change in knee problem, quality of life, physical activity levels, internalized weight stigma, physical performance and quadriceps muscle strength. Additional measures will assess adherence, adverse events, intervention fidelity and a range of process outcomes.

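### Quadriceps strength is recorded only per kg of body mass, so on the natural reading the diet arm's weight loss alone raises the score, and no result in Nm stands beside it

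*Protocol article*

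**What the plan says.** Under Outcome measures, the timing of the secondary outcomes is given as "These are measured at baseline and 6 months, unless otherwise stated". Item xii is isometric knee-extensor strength on a dynamometer, and its scale is fixed: "The maximum torque reached over 3 repetitions of 5 seconds, normalized to body mass, will be recorded in Nm/kg". No outcome in Nm appears anywhere in the article, and the text does not say whether the 6-month torque is divided by 6-month or baseline mass.

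The Background names the construct without reference to body weight, listing "physical performance and quadriceps muscle strength" among the effects to be evaluated.

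The same section that defines the strength outcome also defines the primary one: "Change in body weight, expressed as a percentage, is the primary outcome". The diet plus exercise programme is described as "aiming for ≥10% body weight loss". The Trial sample size section assumes a 5% between-group difference in weight loss, with no weight change under exercise alone. The Data analysis plan compares the primary outcome by linear regression adjusted for baseline weight, sex and physiotherapist, and treats continuous secondary outcomes in a similar way.

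**The concern.** Torque per kg is a sensible scale when body mass is stable or changes equally in both arms. Here mass is meant to fall in one arm and is assumed not to move in the other. If the 6-month torque is divided by 6-month mass, the treatment effect on weight enters the strength score through its denominator. Part or all of any strength difference in favour of diet plus exercise could then be the primary result seen again on another scale.

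Both arms receive the same strengthening programme, so the strength comparison asks what adding the diet does to quadriceps strength. At stake is the reading of that one secondary outcome. A higher Nm/kg in the diet arm could be reported as stronger muscle when torque is unchanged, and a decline in torque could be reported as no effect.

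**Working it through.** **The plan's own figure.** The article gives no figure for the strength outcome. Its planning figures for weight reproduce. With difference 5, SD 7.5, two-sided alpha 0.05 and power 0.80, the normal approximation gives 36 per group. The t-test gives 36.3, so 37 as stated, and 37/0.85 = 43.5, so 44 as stated. The 5% difference can therefore be taken as the design value.

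**Inputs.**
- Weight loss w in the diet arm: 5% (Trial sample size) and 10% (target in the Diet plus exercise program section).
- Weight change in the exercise arm: 0% (Trial sample size).
- Relative change in torque t: not given, so varied.

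**Formula.** With mass taken at the same visit, the relative change in Nm/kg is (1 + t)/(1 − w) − 1.

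**Torque unchanged (t = 0).**
- w = 5%: 1/0.95 − 1 = +5.3%
- w = 10%: 1/0.90 − 1 = +11.1%
- Exercise arm, w = 0: 0%

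These are also the between-group differences, relative to the baseline score.

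**Torque falling.**
- w = 5%, t = −3%: 0.97/0.95 − 1 = +2.1%
- w = 5%, t = −5%: 0.95/0.95 − 1 = 0
- w = 10%, t = −5%: 0.95/0.90 − 1 = +5.6%
- w = 10%, t = −10%: 0.90/0.90 − 1 = 0

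**Spread between participants.** If weight change has the planning SD of 7.5% in both arms and is unrelated to the baseline score, a second-order expansion gives (1/0.95 + 0.075²/0.95³)/(1 + 0.075²) = (1.0526 + 0.0066)/1.0056 = 1.053. The 5.3% therefore does not depend on everyone losing the same amount.

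**Does the planned adjustment remove it?** Take two participants with the same sex, physiotherapist, baseline weight and baseline score S, and with unchanged torque. One loses 10% of body weight on the diet, and the other, in the exercise arm, loses none. Their 6-month scores are S/0.90 and S. The gap of 0.111 × S arises after randomisation, so conditioning on baseline values leaves it in the group coefficient.

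**The other reading.** If torque at both visits is divided by baseline mass, the relative change is (1 + t) − 1 = t, and weight loss has no influence.

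**Would it reach significance?** The article gives neither a baseline mean nor an SD for this outcome. Assuming 1.0 to 1.6 Nm/kg, an SD of 0.15 to 0.35 and 37 per group, the chance of a significant difference with no change in torque runs from 0.095 to 0.675 at 5% weight loss, and from 0.28 to above 0.99 at 10%. These inputs are assumptions and the range is too wide to carry weight, so the conclusion does not use it.

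**The case against.** **The denominator is not stated.** A reader might take it as fact that 6-month torque is divided by 6-month mass. The article does not say so, and with baseline mass the problem vanishes. This stands as a limit on the claim. Weight is measured at both visits, so same-visit mass remains the natural reading, and the silence is itself a reason to name the mass.

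**Relative strength is a real quantity.** Someone with the same torque and less weight to move has gained relative strength, and the unit is stated openly. This also stands: Nm/kg is not invalid. What remains is that it is the only scale given for an outcome described simply as quadriceps strength.

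**Nothing is lost, and the analysis plan could add it.** With same-visit mass, torque is Nm/kg multiplied by kg, and the analysis plan is not shown. True, but the scale is a stated choice and not an omitted detail. A plan that follows it inherits the difficulty, and a result in Nm added after the data are seen would be post hoc.

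**Larger figures are tempting.** The Background says that those adhering to such a diet "frequently achieve a 10–15% weight loss target weight within 12 weeks", and 15% would give a larger inflation. That is the top of a range for adherers at an earlier time, not an expected 6-month arm mean, so it is not used. The 10% figure is likewise a programme target and not a forecast.

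**Safety.** A reader might infer that a hidden loss of strength is a safety failure, since the Discussion names safety among the things the trial will inform. The protocol measures safety through adverse events and does not designate strength as a safety outcome, so that reading is not supported.

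**Conclusion.** The point holds as one of outcome definition and interpretation for a single secondary outcome. If Nm/kg uses mass at the same visit, the intended weight loss alone raises the diet arm's score by 5.3% at the design difference and by 11.1% at the programme target. A fall in torque proportional to the weight loss would appear as no change. The planned baseline adjustment does not correct this. A between-group difference in Nm/kg therefore cannot by itself be reported as a gain in quadriceps strength.

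This rests on the same-visit reading of the denominator and on the article's own weight-loss figures. It does not show that strength falls on this diet: the article has no evidence on that, and both arms do the same strengthening exercises. The primary outcome and the sample size are untouched.

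**What to change.** Before unblinding, in the statistical analysis plan that the article promises to publish while blinded:

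- Prespecify an analysis of peak isometric torque in Nm, adjusted for baseline torque, sex and physiotherapist. Torque at both visits divided by baseline mass would serve equally well.
- Keep Nm/kg beside it, state which body mass is used at each visit, and, if it is same-visit mass, label the result as strength relative to current body weight.
- State that any conclusion about muscle strength will rest on the absolute result.

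Nm/kg need not be withdrawn or replaced. Recruitment began in October 2021, and adding a companion result avoids redefining a published outcome in a running trial. The cost is one extra secondary analysis and a few lines of text. Torque and weight are already measured at both visits, so no new data are needed.
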